**Methods:**

This randomized controlled trial will be performed on a large sample of the employees working in two healthcare centers in the city of Shiraz, Iran. The study will proceed with the healthcare workers of one city being given the educational intervention and the healthcare workers of the other city serving as a control group. Using a census method, all healthcare workers in the two cities will be informed of the trial and its purpose, and then invitations to join the study will be issued. The minimum sample size required has been calculated as 66 individuals in each healthcare centers. Recruitment to the trial will by systematic random sampling of eligible employees who submit an expression of interest in joining the trial, and subsequently give informed consent. Data will be collected through a self-administered survey instrument at three stages: at baseline, and both immediately and three months after the intervention. The experimental group members should participate in at least eight of the ten weekly educational sessions of the intervention and complete the surveys in the three stages. There is no educational intervention for the control group, and they simply experience some routine programs, and complete the surveys at the same three timepoints.

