## Methods

### Study design, setting and participants

This quasi-experimental study is a non-blinded randomized controlled trial (RCT) (Code: IRCT20220509054790N1) with assessments at baseline, immediately after the intervention, and three months after the intervention. This study was approved by the Ethics Committee in Medical Research affiliated to Shiraz University of Medical Sciences, Shiraz, Iran.

Recruitment will be from two large healthcare centers in the northern and southern parts of the city of Shiraz, in southern Iran (namely, Wal-fajr and Enghelab). Permission to undertake the study in these two healthcare centers was sought as they are comparable in their cultural and socio-economic characteristics. This method has previously been used as a means of preventing information exchange between the participants in the experimental and control groups [53]. The two healthcare centers will be randomly assigned to intervention and control settings following recruitment. Using the MedCalc software and the following formula:$$n \ge \frac{{(Z_{{1 - {\raise0.5ex\hbox{$\scriptstyle a$} \kern-0.1em/\kern-0.15em \lower0.25ex\hbox{$\scriptstyle 2$}}}} + Z_{{1 - \beta }} )\left( {\sigma _{1}^{2} + \sigma _{2}^{2} /r} \right)}}{{(\mu _{1} - \mu _{2} )^{2} }}$$

The sample size is estimated to be 66 participants in each group. Considering the 5% loss of observations, the final sample size will be determined to be 69 in each group.

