The study has been advertised in the two healthcare centers, and information about the study distributed to all HCW. Inclusion criteria are being employed at the healthcare center, aged 25–60 years, and no self-reported history of severe physical or mental illness. (This will also be checked again at the community survey stage). Exclusion criteria are severe physical or mental illness, not giving informed consent, reluctance to continue the study/not participating in either intervention and/or surveys. For sampling, first, an alphabetical list of the names of all HCW in both centers is prepared. Thenceforth, the samples will be selected in a randomized manner. If a person is not eligible, or does not give written informed consent, then they will be replaced with the next one available on the list will be replaced. Baseline data will then be collected from all participants. There are no incentives for participating in the research, but also no costs because data collection will be during working time. All participants who complete the study will be given a certificate of participation in the study.

A flow diagram of the RCT protocol is presented in Fig. 1. The control group will have no intervention. During the 10-week intervention period participants in the control group healthcare center will be offered routine staff training opportunities. Participants in the intervention group will receive the intervention described below. The logic model used for the intervention planning and evaluation—the PRECEDE-PROCEED model—is illustrated in Fig. 2. Table 1 shows the key research questions and the data sources according to the model phases.

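### Non-participation in the intervention is listed as an exclusion criterion; it arises after allocation and can remove people from the intervention arm only

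*Protocol article*

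**What the plan says.** In the protocol article, under Study design, setting and participants, the eligibility paragraph reads: "Exclusion criteria are severe physical or mental illness, not giving informed consent, reluctance to continue the study/not participating in either intervention and/or surveys". The same section fixes when allocation happens: "The two healthcare centers will be randomly assigned to intervention and control settings following recruitment". It describes the trial as non-blinded and says that the control group has no intervention; over the ten weeks, "participants in the control group healthcare center will be offered routine staff training opportunities".

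The Methods part of the abstract sets a participation standard for one arm: "The experimental group members should participate in at least eight of the ten weekly educational sessions of the intervention and complete the surveys" at all three stages. For controls it says that "they simply experience some routine programs, and complete the surveys at the same three timepoints".

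The Demographic information section adds a further exclusion, for illness needing medication or psychiatric consultation reported at any of the three time points. It applies to both arms.

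The Data analysis section plans ANCOVA to compare the groups, together with t-tests and, if the data are not normal, Mann-Whitney tests. Nowhere does the article say that people excluded for non-participation are still surveyed or kept in the comparison.

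**The concern.** Eligibility criteria should be decidable before allocation. Reluctance to continue, and failure to take part in an intervention, are behaviours that show only once the trial is under way. Here they are listed beside severe illness and lack of consent as grounds for exclusion.

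The exclusion for not participating in the intervention also falls unequally. An intervention member who stops coming to sessions can be excluded under it. A control member cannot, having no sessions to miss. If staying with the sessions is related to resilience, social capital, wellbeing or lifestyle, or to how these change over the ten weeks, the two analysed groups differ for a reason other than the program. Because participants know their allocation, the decision to stay or leave can also depend on it.

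At stake is the question that the trial answers. The stated aim is the effect of the program in healthcare workers, and the Discussion rests the study's strength on being an RCT. With non-participants removed, the comparison moves toward an effect in those who attended, set against controls who were not selected in that way.

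**Working it through.** **Passages side by side**

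| Ground for removal | Known before allocation? | Can act in intervention arm | Can act in control arm |
|---|---|---|---|
| Not participating in the intervention | No | Yes | No (no intervention) |
| Reluctance to continue | No | Yes | Yes |
| Not participating in follow-up surveys | No | Yes | Yes |
| Illness or psychiatric consultation reported at a later survey | No | Yes | Yes |

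Only the first row is one-sided by construction.

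**The plan's own figures.** The article gives 66 per group, a 5% loss and a final 69. Check: 66/0.95 = 69.47 and 66 × 1.05 = 69.3, so 69 is reproduced to within rounding. The allowance is 69 − 66 = 3 people per group. The base figure of 66 cannot be checked, because its inputs are not given; nothing below depends on it.

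**Illustration of size.** Two inputs are assumptions and are not in the document: q, the share of the intervention arm removed, and ρ, the correlation of engagement with the outcome. Suppose there is no true effect and the least engaged fraction q is removed from the intervention arm only.

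- Spurious difference in SD units: b = ρ × φ(z_q)/(1 − q)
- Standard error: SE = √(1/69 + 1/[69(1 − q)])
- Two-sided 5% rejection rate: 1 − Φ(1.96 − b/SE) + Φ(−1.96 − b/SE)

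Example with q = 0.20 and ρ = 0.3: φ(z_q) = 0.280, and 0.280/0.80 = 0.350, so b = 0.3 × 0.350 = 0.105. The arm falls to 69 × 0.80 = 55.2, SE = 0.181, b/SE = 0.58, and the rejection rate is 9.0%.

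| q | Intervention n left | b, ρ = 0.3 | Type I error | b, ρ = 0.5 | Type I error |
|---|---|---|---|---|---|
| 5% | 65.5 | 0.03 | 5.4% | 0.05 | 6.1% |
| 10% | 62.1 | 0.06 | 6.3% | 0.10 | 8.6% |
| 20% | 55.2 | 0.11 | 9.0% | 0.18 | 16.3% |
| 30% | 48.3 | 0.15 | 12.5% | 0.25 | 26.3% |

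With ρ = 0.1 the error stays between 5.0% and 5.8% over the whole range of q.

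**With baseline adjustment.** Assume further that engagement correlates equally with baseline and follow-up, and that the baseline to follow-up correlation c is 0.5 to 0.7. As an approximation, the ANCOVA bias is b(1− c) and the residual SD is √(1 − c²).

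- q = 20%, ρ = 0.3: 0.105 × 0.5 = 0.05 and 0.105 × 0.3 = 0.03 SD; type I error about 6%.
- q = 30%, ρ = 0.5: 0.248 × 0.5 = 0.12 and 0.248 × 0.3 = 0.07 SD; type I error about 12% and 9%.
- q = 5%: type I error 5.1 to 5.4%.

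These rates treat individuals as independent and isolate this one issue. They leave aside that each arm is a single center.

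**Precision.** Removal of 20 to 30% would leave about 55 to 48 people in the intervention arm, below the 66 that the article requires.

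**The case against.** The strongest case against has five parts.

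1. **The eight-session rule is not an exclusion rule.** A reader might infer that anyone attending fewer than eight sessions is dropped. The abstract only says that members should attend that many, and the eligibility paragraph gives no threshold. Non-participation could mean only those who attend nothing or leave. This stands: the link between the two passages is an inference. The exclusion for not participating in the intervention is explicit without it.

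2. **Controls are filtered too.** A reader might infer that selected attenders are compared with all controls. The document does not support this. Reluctance to continue, missed surveys and the illness rule remove controls as well. This stands, and it limits the asymmetry to session participation.

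3. **The mechanism is assumed.** It is tempting to say that those who attend sessions in working hours are the more resilient and better supported staff. The article places data collection in working time but does not say when sessions are held, and it gives no evidence on who attends. The direction of the bias is plausible but not established.

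4. **The planned analysis adjusts for baseline, and planned loss is small.** The first hypothesis concerns change scores. If engagement correlates equally with baseline and follow-up, that bias cancels in a change score. ANCOVA shrinks it, and at the article's own 5% loss it is slight. This stands as to size. However, adjustment does not remove attrition driven by what happens during the ten weeks, such as rising workload, and the planned t-tests and Mann-Whitney comparisons of scores carry no such adjustment.

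5. **Analysis populations are commonly left to an analysis plan.** This is fair, and the lack of a named analysis set is not the point. The article itself fixes a post-allocation exclusion that works in one arm.

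**Conclusion.** The point holds in a limited form. As written, the eligibility paragraph contains exclusions that can be known only after allocation, and one of them can remove people from the intervention arm alone. Followed literally, it departs from a comparison of groups as allocated. Together with the eight-of-ten expectation, it may restrict the analysed intervention arm to engaged attenders, but the article does not say that it does.

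The size is unknown. It rests on the share removed and on how engagement relates to the outcomes, and the document gives neither. The only loss figure given is 5%, at which the unadjusted bias is about 0.03 to 0.05 SD under correlations of 0.3 to 0.5. The larger figures, about 0.11 to 0.25 SD and 9 to 26% type I error, need 20 to 30% removal and no baseline adjustment. With ANCOVA and a baseline to follow-up correlation of 0.5 to 0.7, they become about 6 to 12%. A reader should not take the upper figures as an estimate of what this trial will show.

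The correction is worth making whatever the size, because outcomes never collected from excluded people cannot be recovered at the analysis stage.

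**What to change.** - Remove non-participation in the intervention or surveys, and reluctance to continue, from the exclusion criteria. Treat them as adherence and missing-data events instead.
- Seek all three surveys from every consenting participant who has not withdrawn consent to data collection, whatever their attendance.
- Make the main comparison by the arm to which each participant's center was allocated, regardless of sessions attended.
- State that attending at least eight sessions is a fidelity measure, and report results in that subset only as a supplementary analysis.
- Because surveys are posted anonymously, use a coded identifier so that attendance can be linked to responses.

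**Cost.** Mostly rewording, plus setting up the coded link and some extra effort to survey people who stop attending. The estimated effect may be smaller than in an attenders-only comparison. Consent withdrawal must still be honoured, so some loss will remain.

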**Fig. 1 Fig1:**
[figure not shown]
CONSORT flow diagram for enrolment and randomization in the study

**Fig. 2 Fig2:**
[figure not shown]
Application of the PRECEDE-PROCEED model

**Table 1 Tab1:** Phases 1–8 of PRECEDE-PROCEED model: the main questions to be addressed and the sources of data

Phase	Main questions to be addressed	Data sources
1. Social assessment	What are the demographic characteristics of the study participants? What is the QoL status of HCW?	Literature review
2. Epidemiological assessment	What are the behavioral risk factors affecting psychological well-being? What are the environmental causes of the health concerns? How is the psychological well-being of the participants?	Literature review Community survey (Measuring psychological wellbeing, health-promoting lifestyle, resilience, and social capital)
3. Educational and ecological assessment	What are the predisposing factors? (Knowledge, self-efficacy, outcome expectation, outcome expectancy, and self-regulation) What are the reinforcing factors? (Social support) What are the enabling factors? (Behavioral skills)	Literature review Community survey (Developing a tool for measuring determinant of resilience based on SCT)
4. Administrative and policy assessment and intervention alignment	What are the procedures, resources, and other capacities in the organization? Which policies, rules, and organizational aspects restrain changes in enabling factors? What are the factors affecting the implementation of the intervention? (Understanding barriers and opportunities)	Interview with key informant of organization
5. Implementation	What are the health promotion strategies per educational objective? Are strategies in line with the aims? What is the deadline for the implementation of strategies? Which resources are required?	Educational intervention
6. Process evaluation	What are the process indicators?	Group discussion Polls form
7. Impact evaluation	What are the impact indicators?	Community survey
8. Outcome evaluation	What are the outcome indicators?	Community survey

### Intervention program

The evaluation program will be based upon the the evaluations from the first three phases and a consideration of the characteristics of the target population. Theories of behavior change such as the SCT we are using to support our educational program, show the focus of the intervention program and propose useful strategies to achieve the goals of change [54]. For example, the concept of self-esteem, and ways to increase it, will be taught to improve self-efficacy. Similarly, the intervention group will be trained with thinking traps and recognizing their thoughts to improve self-regulation skills, in order to control their emotions, as well as speed skills to monitor their emotions. Although there is some diversity in terms of education duration and topics [55] the available evidence suggests that empowering employees in the field of resilience skills is one of the important components of health promotion programs [56]. The effectiveness of an educational program is also dependent upon the application of educational theories, which can support the ability of the material to change the behavior of the target population [57]. Theories that explain adult learning suggest that collaboration and active involvement in the educational sessions are required, as well as positive reinforcement by timely feedback [58]. In view of this, some techniques, such as small-group discussions, role-plays, and questions and answers will be used to support good face-to-face teaching-learning practices. The educational sessions will also include video clips, podcasts, pamphlets and other purposeful handouts to support assimilation of the materials both during the sessions and as homework. This can help increase the learning of more contents during the education process [59, 60].

Drawing on intervention studies that have published their experiences, it seems that an educational program consisting of 8–10 sessions, should be effective in developing basic resilience skills. Similarly, other interventions with educational training in weekly sessions of 60–90 min have been found to have sustainable positive outcomes [53]. Thus, the contents of the intervention program will proceed with 10 sessions, each approximately 60–90 min, with the contents shown in Table 2.

**Table 2 Tab2:** Contents of the educational intervention program sessions

Sessions	Contents
1	Introduction. familiarization with the research objectives, groups, and participants
2	Resilience, familiarity with emotions
3	Cognitive traps
4	Cognitive traps
5	Problem-solving skills
6	Speed skills to control emotions
7	Effective communication skills
8	Effective communication skills
9	Self-esteem and self-efficacy skills
10	Self-esteem and self-efficacy skills

### Data collection and instruments

Data will be collected at three time points from both the intervention group and the control group. A pen and paper survey will be distributed at dedicated times during the working day, according to HCW shift. Time will be set aside for participants to complete their survey, and post anonymously in a sealed collection box. made up for the following instruments:

### Demographic information

A researcher-made questionnaire will be used to collect information regarding participants sex, age, education level, marital status, and history of illness, seeking psychiatric support and taking medication. (Participants who report chronic illness needing medication, or consultations with a psychiatrist who give a positive answer at any of the three time points will be excluded from the study.)

*Social Capital at Work* [61]. This measure is made up of eight items that together assess the cognitive and structural components of social capital at work. Items explore mutual respect and trust between colleagues and a supervisor, reciprocity, participation in networks and collective action. An example is: “People feel understood and accepted by each other”. Answers to the statements are given using a five-point agreement scale where 1 = fully disagree, to 5 = fully agree, and low scores will indicate low social capital. This questionnaire has been reliably used in Iran [62].

*Resilience at Work Scale* [42]. The scale authors assert that resilience is a capability and that the scale supports intervention to support employees develop strengths in these areas to enable them to cope with work challenges. It comprises 20 items that assess seven aspects of resilience at work: living authentically (3 items), finding one’s calling (4 items), maintaining perspective (3 items), mastering stress (4 items), interacting cooperatively (2 items), staying healthy (2 items) and building networks (2 items). Each item is rated using seven-point agreement scale ranging from 1 = completely disagree to 7 = completely agree, and high scores indicate higher resilience. Previous studies have confirmed its reliability [39]. This will also be confirmed in this study through Cronbach’s alpha coefficient and test-retest method.

*Resilience Skills Questionnaire*. This is a 17-item researcher-made questionnaire based on three key constructs of SCT: self-efficacy, self-regulation and reinforcement from social support. Participants respond to each item using a 5-point agreement scale where 1 = strongly disagree, to 5 = strongly agree, and higher scores will indicate better status in each construct. A pilot study in a sample of the statistical population indicated the RSQ has good psychometric properties. This study will confirm its reliability through Cronbach’s alpha coefficient and test-retest method.

*Psychological Wellbeing Scale* [63]. There are various versions of scales to measure the six dimensions of PWB originally identified by Ryff [64]: environmental mastery, personal growth, purpose in life, self-acceptance, autonomy, and positive relations. In this study we used an 18-item version originally designed by Ryff and Keyes [65] and validated in an Iranian sample by Khanjani et al. [63]. There are three items for each of the six dimensions; participants will rate themselves on a six-point agreement scale where 1 = strongly disagree to 6 = strongly agree. Scores on items that are negatively phrased will be reversed so that the higher the total score, the greater the participant’s well-being. Dimensional scores can also be calculated (range 3–18).

*Health-Promoting Lifestyle Profile* [66]. This 52-item questionnaire assesses the extent to which adults engage in health behaviors associated with six dimensions: health responsibility, spiritual growth, physical activity, nutrition, stress management and interpersonal relations. Participants will use the original a four-point frequency scale where 1 = never, 2 = sometimes, 3 = often, to 4 = routinely. The reliability and validity of a Persian version of the scale have been measured by Mohammadi Zeidi et al. [67].

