In the present study, the groundwork for the evidence-based targeted intervention measures that will be implemented and evaluated was provided by a review of the literature to assess the social and epidemiological background of similar HCW populations. This approach implemented the first three phases of the PRECEDE-PROCEED model and was essential to achieve a logical framework for planning the health-promoting intervention and identifying its components. The social, epidemiological, behavioral, and environmental assessment provided by the literature review found evidence that the mental health and QoL of HCW was negatively by their work, particularly since the outbreak of the COVID-19 pandemic [23, 24]. It also confirmed that QoL can be affected by one’s health conditions [25–27]. Psychological wellbeing (PWB) is accordingly one of the determinants of the QoL among employees [28], and it is strongly influenced by one’s psychosocial environment and behavior. Here, wellbeing refers to a concept that defines the quality of work life, as a main determinant of productivity in individuals, organizations, and society [29]. People with low wellbeing may thus evaluate events and situations in their lives as adverse ones, and undergo negative emotions, e.g., anxiety, depression, and anger [30].

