
The third phase of the PRECEDE-PROCEED model is an educational and ecological assessment, wherein the determinants of behavior and environment are typically examined in three categories: predisposing, reinforcing, and enabling factors. Here, predisposing factors include knowledge, attitudes, self-efficacy, outcome expectations, and outcome values; reinforcing factors are perceived social or organizational support, and enabling factors consist of having access to and support of resources and personal skills [22–24]. In different phases of applying the PRECEDE-PROCEED model, especially in the third phase, the specific theories of behavior change related to the research problem and setting can be used [20, 45], which help in augmenting the internal validity of the study. In light of this, the Social Cognitive Theory (SCT) is suitable for the analysis of the problem in the PRECEDE-PROCEED model. This theory can explain human behavior in terms of having three-way causality (individual, environmental, and behavioral) [46, 47], whose interactions can produce behavior change [48, 49].

The fourth phase of the PRECEDE-PROCEED model includes a review of educational programs, policies, and procedures within an organization, and ultimately the intervention program is developed. During the fifth phase, the proposed intervention program is implemented among employees, then in phases six to eight comprise process, impact, and outcome evaluations [21, 22, 24, 50].

To date, interventions to improve resilience towards better health outcomes have lacked a longitudinal element, good outcome measures, and comprise other design issues [51]. Similarly, despite strong assertions that improving social capital can improve health, there is a dearth of intervention studies to examine these claims [52]. In general, it seems that the PRECEDE-PROCEED model integrated into the three SCT factors (individual, environmental, and behavioral) can be exploited as a suitable theoretical framework for the design and evaluation of mental health-promoting interventions among HCW in a longitudinal RCT. Therefore, the aim of this study is to determine the effects of an evidence-based educational program on resilience, social capital, PWB, and HPL in HCW, using the SCT integrated into the PRECEDE-PROCEED model.

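### Reports of medicated illness or psychiatric consultation at the two follow-up surveys exclude workers after allocation, which can bias the comparison between arms in either direction

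*Protocol article*

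**What the plan says.** The Demographic information section describes a questionnaire that includes history of illness, psychiatric support and medication. It attaches an exclusion rule to the answers. The rule starts with "Participants who report chronic illness needing medication" and goes on: "consultations with a psychiatrist who give a positive answer at any of the three time points will be excluded from the study".

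The Study design section fixes the surveys: "with assessments at baseline, immediately after the intervention, and three months after the intervention". The same section assigns the two centers to arms after recruitment. Both later surveys therefore follow allocation and delivery of the programme.

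That section also has an entry criterion, "no self-reported history of severe physical or mental illness", with a note that it will be checked again at the community survey. Its exclusion list repeats severe illness without a time limit and adds "reluctance to continue the study/not participating in either intervention and/or surveys".

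The stated aim is to "determine the effects of an evidence-based educational program on resilience, social capital, PWB, and HPL in HCW". The Background says that people with low wellbeing may "undergo negative emotions, e.g., anxiety, depression, and anger". The lifestyle instrument covers "health responsibility, spiritual growth, physical activity, nutrition, stress management and interpersonal relations". The Data analysis section compares arm means by ANCOVA, or by rank tests if the data are not normal. It names no analysis set that would keep excluded workers in.

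**The concern.** At baseline the illness question is an ordinary eligibility screen. At the two later surveys the same question acts on something that happens after allocation and lies close to what the trial measures. By the document's own account, low wellbeing goes with anxiety and depression, so a new psychiatric consultation is likely to mark a worker with poor wellbeing scores.

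The programme could move the trigger either way. If it prevents illness, more poorly faring controls than intervention workers are removed, and a real benefit is understated. If it makes workers readier to seek help, more poorly faring intervention workers are removed, and a programme with no effect on wellbeing can look beneficial. In both cases the arms are compared after losing different kinds of people, and random assignment does not protect against that.

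The wording removes the person from the study, not from one analysis. A worker positive at the first follow-up may then have no three-month score, and a later analysis plan cannot restore data that were never collected. The point holds whatever illness threshold applies at entry.

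**Working it through.** **The plan's own figures.** The documents give no illness, consultation or exclusion rate. The nearest figure is the 5% loss allowance: 66 × 1.05 = 69.3 and 66/0.95 = 69.5, against a stated 69 per group. That agrees to within one participant and is not in dispute.

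**Assumed inputs.** Outcome SD 1; correlation of baseline with follow-up wellbeing 0.6; no true effect; 5% of controls and 20% of intervention workers removed. The liability to be positive is normal and correlates -ρ with follow-up wellbeing and -ρ_b with baseline wellbeing.

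**Step 1, shift in an arm's mean.** If a proportion p with the highest liability is removed and c = z(1-p), the mean of those retained rises by ρ·m(p), where m(p) = φ(c)/(1-p).
- m(0.05) = 0.1086 and m(0.20) = 0.3500, a difference of 0.2414.
- At ρ = 0.5 the unadjusted false benefit is 0.5 × 0.2414 = 0.121 SD.

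**Step 2, ANCOVA.** Selection also shifts the baseline means if liability is related to baseline wellbeing, and adjustment removes part of the bias. The remaining bias is (difference in follow-up means) - (pooled slope) × (difference in baseline means). Simulation with 2 million per arm at ρ = 0.5 gives:

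| Liability v baseline (ρ_b) | Follow-up difference | Baseline difference | Slope | ANCOVA bias |
|---|---|---|---|---|
| 0 | 0.12 | 0.00 | 0.60 | 0.12 SD |
| 0.3 | 0.120 | 0.071 | 0.571 | 0.079 SD |
| 0.5 | 0.121 | 0.120 | 0.568 | 0.053 SD |

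The value 0.3 is what follows if illness acts only through follow-up wellbeing (0.6 × 0.5).

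**Step 3, error rate.** With 66 per arm, SE = √[(2/66)(1 - 0.36)] = 0.139. Put k = bias/SE; the two-sided error is Φ(-1.96 + k) + Φ(-1.96 - k).
- Bias 0.079: k = 0.57, error about 9%.
- Bias 0.053: k = 0.38, error about 7%.
- Bias 0.121 (liability unrelated to baseline): k = 0.87, error about 14%.

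Using the numbers left after removal (62.7 and 52.8) and the residual SD among those retained, the first two become 8.4% and 6.5%. For ρ from 0.3 to 0.7, with ρ_b between 0.6ρ and ρ, the error runs from about 5.5% to 14%.

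**Step 4, the opposite direction.** Take a true effect of 0.50 SD and let the programme lower the trigger only through wellbeing. With ρ from 0.3 to 0.7, the unadjusted difference among those retained is:
- 5% of controls removed: 0.46 to 0.49 SD
- 10% removed: 0.44 to 0.49 SD
- 20% removed: 0.41 to 0.48 SD

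**Step 5, the null case.** With no effect on the outcome or on exclusion, the simulated difference is zero to within 0.002 SD.

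**The case against.** The strongest reply is that every rate above is assumed. Having 20% of an arm turn positive after a clean baseline screen, within ten weekly sessions and three months, may be far too many, and the protocol allows only 5% loss. The questionnaire also asks about history, so some follow-up positives will be pre-existing illness disclosed late, which the programme did not cause. The eligibility note does foresee a second check at the community survey. All of this stands. It limits what can be said about size, but it does not remove the rule, which makes no distinction between late disclosure and a new event.

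Four stronger readings are tempting, and the documents do not support them.
- A reader might infer that only workers who stayed well are compared, or that anyone who deteriorates vanishes from the results. The rule removes only those who report one of the two triggers; workers whose wellbeing falls without either remain. The flow diagram is not shown, so exclusions may yet be reported by arm.
- A reader might put the error rate at 14% (8% to 23% for ρ from 0.3 to 0.7). That requires illness liability to be unrelated to baseline wellbeing, because it sets an unadjusted bias against a baseline-adjusted standard error.
- A reader might take the upward shift in an arm's mean (0.5 × 0.195 = 0.10 SD with 10% removed) as bias in the effect. With equal removal and no effect, the difference between arms is unbiased.
- A reader might extend the figures to lifestyle. Health responsibility and stress management make a link conceivable, but the calculations concern wellbeing only.

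Finally, with one center per arm, an individual-level test does not start from a true 5% in any case. The error rates show only what this rule would add to a nominal test.

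**Conclusion.** The concern holds as a defect of the stated rule. The text is explicit, two of the three surveys follow allocation and the programme, and nothing elsewhere in the article restricts the exclusion to baseline. It is not an omission that an unseen analysis plan could be presumed to repair.

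The plan permits a bias whose size and sign cannot be known from the documents. Under the assumed 5% v 20% removal with ρ = 0.5, it is about 0.05 to 0.08 SD after baseline adjustment, and up to 0.12 SD if liability is unrelated to baseline. It can equally dilute a real effect, and it is zero if the programme changes neither the outcome nor the chance of exclusion. That the effect will be biased is not established; the design simply gives no protection against it. The likely size is modest, so this is a should-fix.

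**What to change.** In the Demographic information section, delete the words that extend the exclusion to all three surveys. Let only the baseline answer exclude, and state that it is taken before the centers are assigned. In the Study design section, state that the severe-illness exclusion likewise applies only at baseline; otherwise removal after allocation could continue under that criterion.

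At both follow-ups, keep the illness and psychiatry question as recorded data. Continue to survey workers who answer positively, analyse their scores in the arm of their center, and tabulate new positive reports by arm.

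The cost is a short edit in two sections, with no new instruments, survey rounds or participants. The retained sample will be slightly more heterogeneous, and some pre-existing illness disclosed late will stay in. The change has to precede the first follow-up, because scores not collected from excluded workers cannot be recovered.
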